## Methods/design

### Ethics

This study has been approved by the NRES Committee West Midlands, Coventry and Warwickshire (REC Reference 13/WM/0152) and registered with Current Controlled Trials (registration number: ISRCTN41442806).

### Intervention

Two VR environments will be investigated in this study (Figure 1). The first VR environment consists of a simulated natural environment. The second VR environment consists of a simulated urban environment. In both groups, patients will be wearing VR goggles and will use a one-handed controller to navigate the environment.

**Figure 1 F1:**
[figure not shown]
The two VR environments.

A Sony personal 3D viewer headset (Figure 2) will be connected to an Alienware gaming laptop and used to display the VR environment. Participants can walk around in the virtual environment by using a Zeemote JS1 thumb stick controller (Figure 3). This controller is also used to look around, since head tracking of the head-mounted device (HMD) will be switched off.

**Figure 2 F2:**
[figure not shown]
The head-mounted device (HMD).

**Figure 3 F3:**
[figure not shown]
The Zeemote JS1 thumb stick controller.

### Study participants

Eligibility for this study is determined using the following criteria:

#### *Inclusion criteria*

1. All patients who are scheduled to undergo dental treatment for fillings or extractions with a planned maximum treatment length of 30 minutes are eligible to participate in the study.

2. This includes both referred patients and in-house patients.

3. Both patients who need relative analgesia (RA) and patients who are treated without sedation will be included.

4. Patients 18 years or older will be included.

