**Methods/design:**

The effectiveness of VR distraction will be examined in patients 18 years or older who are scheduled to undergo dental treatment for fillings and/or extractions, with a maximum length of 30 minutes. Patients will be randomly allocated into one of three groups. The first group will be exposed to a VR of a natural environment. The second group will be exposed to a VR of an urban environment. A third group consists of patients who receive standard care (control group). Primary outcomes relate to patients’ memories of the dental treatment one week after treatment: (a) remembered pain, (b) intrusive thoughts and (c) vividness of memories. Other measures of interest are the dental experience, the treatment experience and the VR experience.

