### Randomization process

Patients will be allocated to one of the three conditions by computer randomization using the ralloc command in the STATA software package. Randomization will be stratified by sedation (RA; yes or no) and the dentist who performs the treatment (dentist 1 or dentist 2). Randomization will be concealed via sequentially numbered opaque sealed envelopes and will be revealed by the dentist or nurse who will start the VR, immediately prior to commencing the treatment.

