#### *For both patient groups*

Patients will be randomized when they attend their scheduled treatment appointment (that is, after baseline data has been recorded). If a patient decides that he or she no longer wants to participate in the study, the baseline data will be discarded. When undergoing their scheduled dental treatment, patients will be exposed to either one of the VR conditions (natural or urban VR environment) or the control condition (usual care). Standard clinical procedures will be followed and when treatment will be started, patients will either be handed a pair of VR goggles (when assigned to the VR groups) or a pair of protective glasses (when assigned to the standard care group). Patients in the VR groups will receive an explanation of how to use the controller by a member of staff. Heart rate will be monitored during dental treatment by a staff member using a pulse oximeter on a finger of the hand that is not operating the controller. The output of the pulse oximeter throughout the treatment session will be recorded by the dentist or nurse. After treatment, staff will record the treatment characteristics and patient characteristics. The patient will be asked to complete a questionnaire in the waiting room before leaving the dental practice. This questionnaire takes about 10 minutes to complete and consists of four parts; treatment experience, VR experience, dental experience and demographic information. The patient will be provided with an envelope, in which to seal the questionnaire.

One week after treatment, patients will receive a phone call, during which we will ask them about their memories and dental anxiety. This phone call will be made by one of the members of the research team and will take between 5 and 10 minutes. After responding to the questions, patients will be debriefed and will be asked if they would like to receive the results of the study. If patients ask questions regarding their clinical care during this interview, it will be tactfully explained to them that the interviewer is not a clinician and they will be directed to the practice for a response to any such queries.

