#### *Other study parameters*

Effect modifiers and possible confounders are:

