##### Treatment characteristics

• The type of treatment

• The length of treatment

• The treating dentist

• Sedation

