### Data analysis

The data will be recorded and analyzed using SPSS 20.0. All data will be analyzed using an intention-to-treat analysis. Descriptive statistics will be calculated. Discrete variables will be summarized by frequencies or proportions. Continuous variables will be reported as means and standard errors or medians and range (depending on the distribution of the variables). Data will be checked for baseline differences between the treatment arms. If baseline differences do occur for any of the variables, they will be added to subsequent models to compensate for those differences using an analysis of covariance approach.

Analyses of covariance (ANCOVAs) will be performed for each of the outcome measures with VR condition (that is, natural, urban or control) as the independent variable and baseline dental anxiety as the covariate, including planned contrasts to explore specific hypotheses. Contrasts for VR condition will be based on comparisons of VR (both natural and urban environments combined) with the no VR control group (comparison 1), natural VR with urban VR (comparison 2), natural VR with the control group and urban VR with the control group (Table 2 gives an overview of specific predictions being tested).

**Table 2 T2:** Overview of the specific comparisons for each prediction

	**Prediction**	**Comparison 1:**	**Comparison 2:**	**Comparison 3:**
		**virtual reality (both natural and urban environments) vs no virtual reality (control group)**	**natural virtual reality vs urban virtual reality**	**(a) natural virtual reality vs control**

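### Fillings and extractions are pooled, but the scheduled procedure, though listed as a possible confounder, is neither a stratum nor a fixed ANCOVA covariate, at a probably modest cost in precision

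*Protocol article*

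**What the plan says.** Under Inclusion criteria, patients are eligible if they are "scheduled to undergo dental treatment for fillings or extractions with a planned maximum treatment length of 30 minutes". The abstract's wording allows for both procedures in one visit. The booked procedure therefore exists before allocation, because "Patients will be randomized when they attend their scheduled treatment appointment (that is, after baseline data has been recorded").

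The strata are given under Randomization process: "Randomization will be stratified by sedation (RA; yes or no) and the dentist who performs the treatment (dentist 1 or dentist 2"). Procedure is not among them.

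Under Other study parameters, the list introduced by "Effect modifiers and possible confounders are" includes, under Treatment characteristics, "The type of treatment". According to the Procedure section and Table 1, staff record treatment characteristics after treatment.

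Data analysis specifies an ANCOVA for each outcome with VR condition "as the independent variable and baseline dental anxiety as the covariate, including planned contrasts to explore specific hypotheses". The only other route into the model is conditional: "If baseline differences do occur for any of the variables, they will be added to subsequent models to compensate for those differences". The list of effect modifiers and possible confounders is not mentioned again in that section.

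**The concern.** A filling and an extraction may leave different memories a week later, when the three primary outcomes (remembered pain, intrusive thoughts, vividness of memories) are taken. For example, soreness in the days after an extraction could cue thoughts about the visit. That mechanism is an assumption, as the protocol does not discuss it. It does flag treatment type as a factor that may matter.

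If procedure predicts the outcomes and is left out of the model, its variance stays in the error term of every VR comparison. Any chance difference in extraction share between arms then adds to the noise in the estimate. The factor is known before allocation, so this noise can be avoided.

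**Working it through.** **Inputs from the protocol (Sample size):** SD 1.3; two-sided alpha 0.05; power 0.80; 90 patients followed up, 60 VR against 30 control; detectable difference about 0.82 units.

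**Assumed, because the protocol gives neither:** extraction share p = 0.20–0.50; difference d between procedures = 0.25–1 SD, measured in SDs within procedure.

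**Step 1: the plan's own figures.** The standard error is 1.3 × √(1/60 + 1/30) = 0.291. Power at 0.82 is Φ(0.82/0.291 − 1.96) = 0.805. The detectable difference at 80% power is (1.96 + 0.842) × 0.291 = 0.814 (0.823 with the t distribution). For drop-out, 30/0.85 rounds up to 36 per group, or 108. For technical failures, 36/0.92 rounds up to 40 per group, or 120. All of these reproduce.

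**Step 2: variance explained by procedure.** R² = p(1−p)d² / (1 + p(1−p)d²). The lowest case (p = 0.20, d = 0.25) gives 0.01/1.01 = 0.01. The highest (p = 0.50, d = 1) gives 0.25/1.25 = 0.20.

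**Step 3: effect of adjustment.** The residual SD is 1.3 × √(1−R²), and 90 patients act like 90/(1−R²).

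| R² | Example (p, d) | Residual SD | Power at 0.82 | Detectable difference | 90 act like |
|---|---|---|---|---|---|
| 0 | no adjustment | 1.300 | 0.805 | 0.814 | 90 |
| 0.01 | 0.20, 0.25 | 1.293 | 0.809 | 0.810 | 91 |
| 0.04 | 0.20, 0.5 | 1.274 | 0.821 | 0.798 | 94 |
| 0.10 | 0.35, 0.7 | 1.233 | 0.845 | 0.773 | 100 |
| 0.20 | 0.50, 1 | 1.163 | 0.884 | 0.728 | 112.5 |

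R² here means what procedure explains beyond baseline anxiety. If the two overlap, the gain is smaller.

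**Step 4: if the pilot SD contains no procedure variation.** The 1.3 is based on a simulation pilot, so real procedures may add variance. With a difference of D units, the unadjusted SD is √(1.69 + p(1−p)D²). For p = 0.20–0.50, D = 0.5 gives power 0.796–0.791 and D = 1 gives 0.769–0.749. Adjustment would return these to about 0.805.

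**Step 5: chance imbalance.** The SD of the gap in extraction share (60 versus 30) is √(p(1−p)(1/60 + 1/30)). This is 0.089 at p = 0.20 and 0.112 at p = 0.50, or 9–11 percentage points. A gap above 10 points arises in about 26–37% of trials, and one above 20 points in about 3–7%. Stratifying by sedation and dentist would lower these figures if extractions cluster by either factor.

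A 10-point gap with a 0.5 SD effect shifts the estimate by 0.10 × 0.5 = 0.05 SD. That is 0.065 units, or 8% of 0.82. A 20-point gap with a 1 SD effect shifts it by 0.20 SD, or 0.26 units (32%), but this pairs an uncommon gap with the largest assumed effect.

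**Step 6: would the baseline-difference rule catch it?** No threshold is given. If a 5% test were used, a 20-point gap would give z = 0.20/SD, which is 2.24 at p = 0.20, 1.95 at p = 0.30 and 1.79 at p = 0.50. Only the first passes 1.96.

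**The case against.** The strongest reply is that nothing here is stated wrongly. Pooling is an eligibility choice, and two stratification factors are a reasonable limit for three arms and 120 patients. Treatment type is collected and flagged, the analysis section already provides for adding variables that differ at baseline, and further model detail may sit in a fuller document.

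Much of this stands. The rule for baseline differences is a real provision, aimed at the large imbalances that would matter most, and adding procedure as a stratum would split the sample into eight cells. However, the article does not leave the model open. It names the covariate for every outcome and omits a factor from its own list. The rule depends on the observed data, and it is arguable whether a variable recorded after treatment counts as baseline. When the arms are balanced it leaves the procedure variance in the error term.

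A reader might also infer that the VR comparison is confounded by procedure. The documents do not support this: allocation is randomized and concealed, so a chance gap is part of sampling error and not a bias. Nor do they support ranking procedure among the strongest predictors of the primary outcomes, since they give no data on its effect.

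**Conclusion.** The point holds as a matter of precision. A factor known before randomization, and recognized by the protocol as potentially important, has no fixed place in the design or the model, and the conditional rule does not make up for that.

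Under the assumed ranges, adjustment raises power from about 0.805 to between 0.81 and 0.88. I judge R² of 0.04–0.10, hence power of 0.82–0.85, the more plausible range, but the protocol cannot confirm it. If procedure has little effect on memories, the gain is close to nil.

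Two stronger readings should be resisted. The sample size is not wrong on its own inputs, because its figures reproduce. A shift of a third of the target difference is also not the expected consequence of imbalance; it needs a gap reached in only about 3–7% of trials together with the largest assumed effect.

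**What to change.** Add one sentence to Data analysis: scheduled procedure (filling only versus any extraction, as booked before the envelope is opened) enters the ANCOVA of the primary and treatment-experience outcomes as a fixed covariate alongside baseline dental anxiety, whatever the observed balance. The category of any extraction covers patients booked for both. Use the booked procedure, because the type recorded after treatment could reflect changes made during the visit.

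Leave the randomization as it is. Enrolment had begun, with two patients randomized at submission, and a covariate needs no change to the allocation scheme.

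The cost is one degree of freedom and one binary field. That field is a small addition to data capture: the staff sheet records type only after treatment, and the article does not describe the booking record as a data source.

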#### *Exclusion criteria*

1. Patients who need intravenous sedation cannot participate in the study.

2. Patients who have previously had epileptic seizures cannot participate in the study, owing to the very small risk that an episode can be triggered by using the HMD, similar to the episodes that might be triggered by watching television.

3. If a patient is scheduled for more than one treatment during the trial period, the patient will only be included for the first treatment.

### Randomization process

Patients will be allocated to one of the three conditions by computer randomization using the ralloc command in the STATA software package. Randomization will be stratified by sedation (RA; yes or no) and the dentist who performs the treatment (dentist 1 or dentist 2). Randomization will be concealed via sequentially numbered opaque sealed envelopes and will be revealed by the dentist or nurse who will start the VR, immediately prior to commencing the treatment.

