### Sample size

Given the novel approach of this study, there is little comparable research available to use for a sample size calculation. We are also somewhat restricted by the number of potential patients available within a given time period in the dental practice. However, we do have data from our own pilot work in a simulated dental setting, which we have used to make an informed estimate of the required sample size for the current study.

The sample size calculation (with a power of 0.80, significance level of 0.05 and based on 2-sided testing) is based on one of the main outcomes related to memories, ‘intrusive thoughts’, as measured with an 11-point verbal rating scale. In our pilot study, the standard deviation for this outcome in our control group was 1.25 and we have conservatively used an estimated standard deviation of 1.3 in this sample size calculation. Based on these assumptions, and comparing the two VR groups against the control group, following up a total sample size of 90 patients (that is, 30 per group) would allow the detection of a between-group difference of around 0.82 units (that is, a moderate effect size). Since drop-outs are unavoidable when collecting follow-up data, this number needs to be adjusted for the estimated drop-out rate. In our simulation study, we had a drop-out rate of 10% for collecting the follow-up data, but since we paid participants for participation in that study (although they received their pay after the simulated treatment and before participating in the follow-up interview), we anticipate a higher drop-out rate for this study, and have allowed for a 15% drop-out rate. Adjusting the sample size for this drop-out rate results in a sample of 108 patients needing to be recruited.

The use of technical computer equipment is associated with the risk of technical failures. In the pilot study we had to exclude 6 of 75 participants because the VR crashed or the remote stopped working during the simulated treatment and the participant was no longer able to interact with the VR environment. Several improvements in the VR program have been made since, such as putting force fields in place that restrict the area of virtual exploration, but we still anticipate the exclusion of participants because of technical issues. We will therefore increase the sample size by a further 8%, resulting in a total recruitment target of 120 for this study (that is, 40 patients per group).

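### The stated ANCOVA leaves out both stratification factors; if sedation or dentist predicts outcome, standard errors are larger than needed and tests conservative

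*Protocol article*

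**What the plan says.** Under Randomization process, the protocol article states: "Randomization will be stratified by sedation (RA; yes or no) and the dentist who performs the treatment (dentist 1 or dentist 2"). That makes 2 x 2 = 4 strata.

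Under Data analysis, the model for each outcome is an ANCOVA "with VR condition (that is, natural, urban or control) as the independent variable and baseline dental anxiety as the covariate". Neither stratification factor is named. The same section has one route for further covariates: a variable on which the arms are found to differ at baseline is added to later models.

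Under Other study parameters, the treating dentist and sedation are listed (as treatment characteristics) among the possible confounders and effect modifiers. The article therefore accepts that they may be related to outcome, but gives no figure for how strongly.

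**The concern.** Design and analysis do not match. Stratified allocation makes the arms alike on sedation and dentist, which reduces the true sampling variance of a treatment contrast if those factors predict outcome. A model without them leaves their variation in the residual, so the standard error it reports does not reflect that reduction. Intervals are then wider than the design warrants, and the tests reject a true null less often than 5% of the time.

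The baseline-difference rule does not close the gap. Factors balanced by stratification will seldom trigger it, and if one did by chance, the adjustment would depend on the data rather than on the design.

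What is at stake is efficiency. The trial expects about 30 patients per arm at follow-up, and the Sample size section says that the supply of patients is limited, so precision cannot easily be bought with more recruitment.

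**Working it through.** **Inputs from the Sample size section.** Error rates: "with a power of 0.80, significance level of 0.05 and based on 2-sided testing". SD: "we have conservatively used an estimated standard deviation of 1.3 in this sample size calculation". Difference: "would allow the detection of a between-group difference of around 0.82 units". Analysed number: "following up a total sample size of 90 patients (that is, 30 per group"). Contrast: "comparing the two VR groups against the control group", read as 60 VR patients against 30 controls. Drop-out: "have allowed for a 15% drop-out rate", followed by a further 8% for technical failures.

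**Assumed input.** R², the share of outcome variance that sedation and dentist explain beyond anxiety. The article does not give it; 0 to 0.30 is used.

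**Reproducing the plan's figures.** SE = 1.3 x sqrt(1/30 + 1/60) = 0.2907. Detectable difference = (1.960 + 0.842) x 0.2907 = 0.814, against the stated 0.82. Power at 0.82 = Φ(0.82/0.2907 - 1.96) = 0.805 (0.797 with the noncentral t). Reading the contrast as 30 against 30 does not fit: it gives a detectable difference of 0.94 and power 0.685. Recruitment: 30/0.85 = 35.3, so 36 per group and 108 in all; 36/0.92 = 39.1, taken to 40 per group and 120 in all. The stated figures hold.

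**Effect of leaving out the strata, with exact balance.** The true SE is sqrt(1 - R²) times the SE that the stated model reports. With SE = 0.2907:
- actual type I error without the factors = 2 x (1 - Φ(1.96/sqrt(1 - R²)))
- power without the factors = Φ((0.82 - 1.96 x SE)/(SE x sqrt(1 - R²)))
- power with the factors = Φ(0.82/(SE x sqrt(1 - R²)) - 1.96)

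Example, R² = 0.20: sqrt(0.80) = 0.894 and the true SE is 0.260. Type I error = 2 x (1 - Φ(2.191)) = 0.028. Power without = Φ(0.250/0.260) = 0.832. Power with = Φ(3.154 - 1.96) = 0.884.

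| R² | Reported SE too large by | Type I error without | Power without | Power with |
|---|---|---|---|---|
| 0 | 0% | 0.050 | 0.805 | 0.805 |
| 0.05 | 2.6% | 0.044 | 0.812 | 0.825 |
| 0.10 | 5.4% | 0.039 | 0.818 | 0.845 |
| 0.20 | 11.8% | 0.028 | 0.832 | 0.884 |
| 0.30 | 19.5% | 0.019 | 0.848 | 0.921 |

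A simulation of 20,000 trials with exact balance agrees. At R² = 0.20, type I error is 0.029 without the factors and 0.051 with them, and power is 0.820 and 0.876.

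**Allowing for the planned loss.** The plan expects 120 randomized to become 90 analysed, a loss of 30/120 = 25%. Loss after randomization disturbs the balance within strata, so the table overstates the conservatism. Simulating 120 patients randomized in 4 strata with 90 analysed gives:

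| R² | Actual type I error without the factors | Power points forgone |
|---|---|---|
| 0 | about 5% | about 0 |
| 0.05 | about 4.5-5% | about 1 |
| 0.10 | about 4.2% | about 3 |
| 0.20 | about 3.7% | about 6 |
| 0.30 | about 2.7% | about 9 |

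At R² = 0, power is 79.7% without and 79.3% with the factors, so the two extra terms cost almost nothing when they do not help. The second table is the one to rely on.

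**The case against.** **The loss is conditional.** It exists only if the factors predict outcome once anxiety is in the model. Baseline anxiety may already absorb part of any sedation effect, so 20% or 30% beyond anxiety is the generous end of the range. This stands, and it is why the range starts at 0%. The calculation also uses the SD of 1.3 without reducing it for the anxiety covariate, so the power figures are approximate.

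**The article is condensed and does not rule the factors out.** It lists both as possible confounders and allows any imbalanced variable into the models. This stands only in part. The article states a model, its covariate and the rule for adding others. The point concerns that stated choice, not a detail left to the SAP.

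**Stronger readings that the documents do not support.** A reader might infer that false positives are inflated or the estimates biased; the error runs the other way, with type I error at or below 5%. A reader might infer that the trial falls short of its planned power or that stratifying was wasted. On the article's own SD, power without the factors stays at about 80% or above, and part of the gain from stratifying is kept. The shortfall is relative to the better model only. A reader might also take type I error to be 3.9%, 2.8% or 1.9% at R² of 0.10, 0.20 or 0.30; those values need exact balance among analysed patients, which the plan's own allowance for loss contradicts.

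**Conclusion.** The mismatch is real: allocation is stratified by two factors that the stated model omits, and the baseline-difference rule will rarely restore them. The consequence is a possible loss of efficiency of unknown size. It is nil if the factors are not prognostic, about 1 power point at R² = 0.05, and up to about 9 points at R² = 0.30, with tests conservative by up to about 2.3 percentage points (5% - 2.7%).

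These figures apply to pooled VR against control at 0.82 units. They rest on a total SD of 1.3, random loss from 120 to 90, and an R² range that is assumed, not documented. The validity of the planned analysis is not in question. The change is worth making because it costs almost nothing and may help appreciably.

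**What to change.** Prespecify sedation (RA yes or no) and treating dentist (1 or 2) as fixed factors in every ANCOVA, alongside VR condition and baseline dental anxiety, regardless of observed balance. Do not leave their inclusion to the baseline-difference rule.

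The cost is 2 degrees of freedom. Both variables are already recorded as treatment characteristics, so no new data are needed. Trial status reports two patients randomized at submission, so at that point the change could be fixed well before outcomes are analysed.

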#### *Overall hypotheses:*

1. Virtual reality exposure will lead to less intrusive thoughts, less vivid memories, less remembered pain and better overall dental experiences.

2. Dental anxiety will moderate the proposed effects under hypothesis 1. Patients with more dental anxiety will benefit more from the use of VR than patients with less dental anxiety.

3. The natural VR environment will be more effective than the urban VR environment.

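### The randomization rule lets the treating dentist open the envelope, so it does not protect a feasible dentist blind to natural versus urban VR

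*Protocol article*

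**What the plan says.** All references are to the protocol article.

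- **Randomization process.** "Patients will be allocated to one of the three conditions by computer randomization", stratified by sedation and by "the dentist who performs the treatment (dentist 1 or dentist 2"). Before use, "Randomization will be concealed via sequentially numbered opaque sealed envelopes". The allocation "will be revealed by the dentist or nurse who will start the VR, immediately prior to commencing the treatment".
- **Intervention.** On the two VR groups: "In both groups, patients will be wearing VR goggles and will use a one-handed controller to navigate the environment". The headset "will be connected to an Alienware gaming laptop and used to display the VR environment".
- **Procedure, For both patient groups.** "The output of the pulse oximeter throughout the treatment session will be recorded by the dentist or nurse". An unspecified staff member explains the controller. Patients fill in the post-treatment questionnaire in the waiting room and are given an envelope to seal it in. A member of the research team telephones one week later.
- **Overall hypotheses.** Hypothesis 3: "The natural VR environment will be more effective than the urban VR environment". Table 2 assigns the natural-versus-urban contrast (comparison 2) to this hypothesis and, among others, to additional predictions 1-5, 7 and 8.

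No sentence says that the dentist is to be kept unaware of which environment is running.

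**The concern.** The dentist will see whether a patient wears VR goggles or protective glasses, so comparison 1 is necessarily open to the dentist. Comparison 2 is different: the two VR groups look alike from outside, and the person giving the care need not know which scene is shown. The rule nevertheless allows that person to open the envelope and start the environment.

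The direction of the expected result is written into the hypotheses. A dentist who knows the scene could, without intending to, reassure, talk or pace the work differently between the two VR arms. Pain, discomfort and stress reports can respond to that. A natural-versus-urban difference would then be harder to attribute to the content of the VR, which is the trial's third aim. Stratifying by dentist balances who treats each arm. It does not stop the same dentist from behaving differently between arms.

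**Working it through.** The point rests on the text, so the first five steps set the sections side by side. The last step checks the only figures that touch it.

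1. **Who may open the envelope?** The dentist or the nurse, whichever starts the VR. The sentence on stratification speaks of the dentist performing the treatment, so the dentist meant here is most naturally the treating dentist. That is a reading of the text; the article does not say it outright.
2. **What does the opener learn?** Randomization is to three conditions, so the opener learns natural, urban or control, not merely VR or no VR.
3. **Could the dentist otherwise stay unaware?** The Intervention section describes goggles and a one-handed controller for both VR groups, so the patient's outward appearance need not give the scene away. The scene is generated on a laptop. The article does not say what its screen shows or whether it can be seen from the chair.
4. **Is another opener available?** Yes. The same sentence already permits the nurse.
5. **Which outcomes are exposed through the dentist's conduct?**
   - *Directly*, during or just after treatment: pain, discomfort, self-reported stress, heart rate, the time estimate, dental anxiety measured straight after treatment, and revisit intention. These are additional predictions 1-5, 7 and 8. Heart rate carries a second exposure, because the dentist or nurse who records it may know the environment.
   - *Indirectly*: intrusive thoughts, vividness and remembered pain. These are collected a week later by the research team, so any effect has to run through the treatment experience.
   - Additional predictions 9 and 10 also use comparison 2, but they are ratings of the virtual environment itself and are not part of this point.
6. **Figures.** The Sample size section gives a detectable difference of about 0.82 on intrusive thoughts (SD 1.3, power 0.80, two-sided 0.05, 30 per group, two VR groups against control).
   - Reproduction, 60 versus 30: (1.960 + 0.842) × 1.3 × √(1/30 + 1/60) = 0.81 by the normal approximation, 0.82 by the t distribution. This agrees with the article.
   - Natural versus urban, 30 versus 30, same assumptions: (1.960 + 0.842) × 1.3 × √(2/30) = 0.94 (0.96 by t).
   - Recruitment: 30/0.85 = 35.3, so 36 per group and 108 in all; 36/0.92 = 39.1, so 40 per group and 120 in all. This also agrees.
   - The two VR arms are 2 × 40 = 80 of the 120 recruited. Who opens the envelope enters none of these calculations.

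**The case against.** The strongest reply is that nothing is shown to go wrong. The nurse is already a permitted opener, so under the present text the dentist may stay unaware for every patient. The dentist neither collects nor scores the questionnaires: patients complete them in the waiting room and are given an envelope to seal them in, and the main memory outcomes go by telephone to the research team. Standard clinical procedures apply in all arms. The document offers no evidence that dentists treat two goggled patients differently according to the scene.

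Much of this stands, and it rules out several stronger readings.

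- *That the trial gives up the blind.* The text permits the unblinding; it does not require it.
- *That the blind is free, or that masking the dentist would make background care identical.* The nurse and the patient would still know the scene, and the patient might mention it. The Sample size section expects some technical failures, which could bring staff to the laptop during treatment.
- *That allocation concealment is defective.* The envelopes are sealed, opaque and numbered, and they are opened only just before treatment. Nothing here weakens that.
- *That the bias can be scaled against 0.82.* That figure belongs to pooled VR versus control. The matching figure for natural versus urban is about 0.94, and the document gives no size for a shift due to care.

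What the reply does not answer is that sealed questionnaires prevent interference with the answers, not an influence on the experience being reported. Following standard procedures does not cover conversation or reassurance. A rule that expressly allows the caregiver to learn the allocation is also not a detail left to a fuller document.

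**Conclusion.** The point holds as a modest design weakness. The randomization rule does not reserve the envelope for someone other than the treating dentist, and so leaves unprotected a dentist blind to natural versus urban that looks feasible. It bears on comparison 2 for hypothesis 3 and additional predictions 1-5, 7 and 8, in 80 of the 120 patients to be recruited. It is most relevant to the outcomes taken at the visit and only indirectly relevant to the one-week memory outcomes. Comparison 1, the concealment procedure and the sample size are unaffected.

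The size of any bias cannot be estimated from the document. The conclusion assumes that the dentist named as a possible opener is the treating dentist, that a nurse is available to start the VR, and that the laptop screen can be kept out of the dentist's sight. The article confirms none of these three. This is an inexpensive improvement, not an error that invalidates the comparison.

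**What to change.** In *Randomization process*, state that the nurse, not the treating dentist, opens the envelope, starts the VR and keeps the laptop screen out of the dentist's view, and tells the dentist only whether the patient has VR or not.

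In *Procedure, For both patient groups*, state that heart rate is taken from the device's stored output where possible, not from a reading by someone who knows the environment. The article does not say whether the oximeter stores its output, so this needs checking. Moving the reading to the operating dentist is not a practical substitute, since the output is wanted throughout the session.

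The cost is a sentence or two in the protocol and a nurse who is free at the start of each treatment. It adds no new role and no patients. The blind will be partial: the nurse and patient know the environment, and a remark or a technical failure may reveal it. Trial status reports only two patients randomized at submission, so a change made then would have covered nearly all of the recruitment.
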